In the Bayesian model, we used weakly informative conjugate gamma priors for the control hazard rate and weakly informative conjugate normal priors for the log-HR. Parameters for the prior distribution of the hazard rate were chosen such that these mirror the hazard rate of the control arm. The prior distribution for the log-HR had a mean of 0 and standard deviation of 5, which is considered to be a weak prior. All scheduled interim analyses estimate the Bayesian posterior probability of an HR of <0.9, and the corresponding stopping boundaries are listed in Table 2. For example, after 350 patients have been randomised, the trial will stop for futility if the posterior probability for HR <0.9 drops below 0.06. With these settings, 10 000 trial simulations were performed in FACTS (5000 for the scenario under the null hypothesis with HR = 1 and 5000 under the alternative scenario with HR = 0.7975). The results of these simulations revealed that the Bayesian empirical type I error rate of the trial was 5.6% and that the empirical power was 76%, to detect a Bayesian posterior probability of ≥75% for an HR of <0.9, during the final analysis under the alternative hypothesis. Importantly, the final one-sided frequentist log-rank test had a power of 79.8% under the alternative hypothesis that the HR is <1 (as opposed to <0.9 in the Bayesian interims) and a frequentist type I error rate of 4.9%. The average sample size was 548.6 in case of an HR of 1 and 596.8 in case of an HR of 0.7975. Notably, a standard two-arm trial without interim analyses would require 700 patients in total.

We also ran 10 000 simulations using an HR of 0.84, simulating a weaker HR due to a higher control dilution and noncompliance (ie, respectively, 15% and 25%) and thereby a lambda of 0.0042 in the control arm. In this scenario, we modelled a maximum of 1000 patients, with interim analyses of 350, 450, 550, 650, 750, 850, and 950 patients and adjusted boundaries as summarised in Table 2. All other settings were kept unchanged. The results of this scenario are still satisfactory, and can be implemented after the measurement of control dilution and noncompliance at the second interim. The Data and Safety Monitoring Board (DSMB) will convey after this interim and is responsible for the decision whether to adapt the maximum sample size of the study at this point. Under the HR = 0.84 assumption, the overall Bayesian type I error rate was 4.3% and the empirical power was 69.1% to detect a posterior probability of 70% for HR >0.9. The average sample size was 869 patients under the null scenario (HR = 1) and 892.4 under the alternative scenario (HR = 0.84). The final frequentist log-rank test had a power of 78.6% and a type I error rate of 5.3%.

### Analysis plan

2.8

Analyses are conducted on an ITT basis. An ITT analysis in a TwiCs study represents the average causal effect of offered treatment, and the intercurrent event noncompliance in the experimental intervention arm is handled according to the treatment policy strategy [31]. At the interim analyses, provisional efficacy will be concluded when the posterior probability of HR <0.9 exceeds the efficacy stopping boundaries, as listed in Table 2. If this happens at an interim analysis, recruitment is stopped, but follow-up is continued. The trial will stop for futility as soon as an interim analysis reveals that the posterior probability for an HR of <0.9 drops below the futility stopping boundaries, as listed in Table 2.

If the maximum sample size has been reached or accrual has been halted based on the efficacy stopping rules, a final analysis will be conducted using the log-rank test for OS after the completion of 5-yr follow-up for all patients. Efficacy of the experimental intervention at the final analysis will be concluded when the one-sided *p* value of this final log-rank falls below 0.05. The OS curve will be constructed using the Kaplan-Meier method. In addition, a per-protocol analysis will be performed. Moreover, ITT and per-protocol subgroup analyses will be performed for subgroups based on the type of local treatment and type of systemic treatment.

In addition, Fisher exact test will be used to compare the treatment arms on objective response rate and surgical morbidity. Follow-up QoL will be assessed by linear mixed models adjusting for baseline score, including treatment group and time as fixed covariates and treating patients at random.

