### Eligibility criteria

2.4

At enrolment in the PRO-RCC cohort, patients are asked to provide informed consent for prospective collection of clinical, survival, and QoL data. In addition, on entry in the cohort, we ask patients to consent for possible future randomisation in TwiCs studies (staged informed consent procedure) [29]. Herein, patients are informed that, when a TwiCs study to investigate the efficacy of a new experimental intervention is initiated, they will be offered that experimental intervention if they are selected randomly for the experimental intervention group. They are also advised that they will not be informed about the TwiCs study when selected randomly for the control group but that their data will be used as in the trial context. Patients within the PRO-RCC cohort who meet the PrimerX inclusion criteria, as mentioned in Table 1, form a subcohort of eligible patients. Within this subcohort, patients without progression at metastatic sites, with the primary tumour in site (irrespectively of the size of the tumour), following at least 6 mo of any of the standard first-line ICI combination therapies, are allocated randomly to either the experimental arm or the control arm in a 1:1 ratio, until the calculated sample size is reached or early stopping rules are met. Patients who have progression in the primary tumour only are also eligible for trial participation. Since patients are randomised at different time points, between 6 and 18 mo after the start of systemic treatment, the timing of randomisation is added as a variable when conducting the analysis.

**Table 1 t0005:** Inclusion criteria

Male or female patients age ≥18 yr
Signed and written informed consent obtained; note: written and signed informed consent will be obtained before any study procedures, including study‐specific-screening procedures
Informed consent obtained for being offered future experimental interventions within the PRO-RCC project
Histologically confirmed diagnosis of metastatic clear cell, papillary, or chromophobe renal cell carcinoma of intermediate to poor risk, including sarcomatoid features
World Health Organization performance status of 0–1
Surgical candidates based on surgeon and anaesthetist assessment
Treatment with an IO combination (IO + IO or IO + TKI) as standard of care for metastatic RCC for at least 6 mo
Absence of progression at metastatic sites at the time of identification (6 mo after the start of systemic first-line treatment)

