### Sample size calculation and Bayesian adaptive design

2.7

Estimation of the median OS of the selected subcohort for PrimerX is not trivial. Based on the CARMENA trial, synchronous mRCC patients treated with sunitinib without CN have median OS of 18.4 mo. All CARMENA patients were treated with VEGFR TKIs only, as ICI combination therapy was not available at the time. In these patients, a reduction in the hazard of death of 20–40% (if they would have been treated with ICI combination therapy, based on the CheckMate-214 study) would have resulted in median OS of 24–28 mo. This is in line with the post hoc OS analysis of mRCC patients with the primary tumour in place in the CM-214 study [30]. This demonstrated median OS of 26.1 mo (95% confidence interval [CI] 14–35 mo) for the ipilimumab + nivolumab arm versus 14.3 mo (95% CI 9.7–23 mo) for the sunitinib arm.

We therefore assume that the median OS for IMDC intermediate/poor-risk synchronous mRCC patients may be up to 28 mo. As in the PrimerX study patients with early systemic disease progression (within 6 mo) are excluded from participation, we estimate that the remaining patients have median OS of 36 mo, when treated with the SOC. The median OS of 36 mo comes down to an event rate per week (lambda) of 1 – (0.5^[1/156 wk]) = 0.0044. We believe that a meaningful deferred local therapy should reduce the hazard of death by at least 25% compared with the SOC (hazard ratio [HR] of 0.75), that is, a 12-mo survival benefit. This would balance the additional treatment burden of local therapy and would result in a median excess in OS of 48 mo in the experimental arm. Furthermore, we estimate that one out of six patients (15%) who are randomised to the experimental arm will refuse any form of local therapy and will therefore be treated by the SOC instead. This noncompliance reduces the measured benefit in an ITT analysis. In addition, a number of patients in the control arm will undergo CN. This also reduces the measured benefit. Based on our 2018–2020 IKNL dataset, we estimate that such “control dilution” will occur in approximately 7% of the cases, as over this period 60 out of 754 synchronous mRCC patients underwent deferred CN. Both noncompliance and control dilution reduce the anticipated HR from 0.75 to 0.7975. After correcting for control dilution, the lambda of the control arm drops from 0.0044 to 0.0043.

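### The deciding log-rank for OS carries neither risk group nor timing of randomisation, although one is known at entry and section 2.4 promises the other; a stratified or adjusted test would protect power at no cost in patients

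*Protocol article*

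**What the plan says.** Section 2.8 (Analysis plan) fixes the final test: "a final analysis will be conducted using the log-rank test for OS after the completion of 5-yr follow-up for all patients". Efficacy is concluded when the one-sided p "value of this final log-rank falls below 0.05". No strata or covariates are named for this test. In the same section, type of systemic treatment appears only as a subgroup factor, and the quality-of-life model does list its covariates.

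Section 2.4 (Eligibility criteria, Table 1) admits "metastatic clear cell, papillary, or chromophobe renal cell carcinoma of intermediate to poor risk, including sarcomatoid features" and requires "Treatment with an IO combination (IO + IO or IO + TKI) as standard of care for metastatic RCC for at least 6 mo". Both risk group and type of combination are therefore known before a patient is randomised. The text of section 2.4 describes 1:1 allocation without naming a stratification factor. It also says that, because patients are randomised at different times between 6 and 18 months after starting systemic treatment, that timing will be a variable in the analysis. Section 2.8 does not take this up.

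Section 2.7 (Sample size calculation and Bayesian adaptive design) gives the planning inputs: "Both noncompliance and control dilution reduce the anticipated HR from 0.75 to 0.7975" and "the lambda of the control arm drops from 0.0044 to 0.0043". From these, "the final one-sided frequentist log-rank test had a power of 79.8% under the alternative hypothesis". One hazard is given for the whole control arm.

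**The concern.** There are two linked problems.

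- **Sections 2.4 and 2.8 do not fit together.** A log-rank without strata compares two arms and takes no covariate. If timing of randomisation belongs in the analysis, the deciding test as written cannot hold it.
- **The test leaves out a prognostic factor that is available at no cost.** When patients differ in baseline risk, the higher-risk patients die earlier, and faster in the control arm. The risk mix of those still at risk then drifts apart between arms, and the unadjusted comparison is pulled towards no effect. A test stratified by risk group compares like with like and avoids most of this.

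What is at stake is a few points of power in a design with no reserve. The target is 80%, and the stated power is 79.8% at a maximum of 700 patients and 78.6% in the fallback scenario with a maximum of 1000.

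**Working it through.** **Inputs from the document (sections 2.7 and 2.8).** HR 0.7975; control hazard 0.0043 per week; 350 patients per arm; one-sided alpha 0.05; 5 years of follow-up after the last patient; Table 2 boundaries for the Bayesian looks at 250 to 650 patients; log-HR prior with SD 5.

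**Assumptions, because the document does not give them.** Accrual time; poor-risk share 20% or 35%; poor-versus-intermediate hazard ratio 1.5, 2.0 or 2.5; a 50/50 split of ICI types with hazard ratio 1.15 or 1.3; no loss to follow-up; HR 0.7975 taken as the effect within each risk group.

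**Step 1: reproduce the plan's power.**

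- Events needed (Schoenfeld): 4 × (1.645 + 0.842)² / (ln 0.7975)² = 4 × 6.183 / 0.0512 = 483.02, so 484.
- Expected events with exponential survival and uniform accrual: 467, 488 and 506 for 1, 2 and 3 years of accrual.
- Power = Φ(√events / 2 × 0.2263 − 1.645) = 78.8%, 80.4% and 81.6%.

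So 700 patients and about 80% power reproduce as a one-sided fixed design. With the five Bayesian looks simulated (normal approximation to the posterior) and accrual of 5 to 7 years, log-rank power was 77-79% if futility stops count as failures and 80-81% if they do not. Average sample size was 591-597 under the alternative and 544-554 under the null. The plan states 79.8%, 596.8 and 548.6. The stated figure is therefore consistent with its own single-hazard inputs.

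**Step 2: let the risk groups differ.** The overall control median was held at ln 2 / 0.0043 weeks. Each simulated trial was tested with the plain and the stratified log-rank (8000 trials per row, Monte Carlo error about 0.5 points per power). In the adaptive columns the looks stay unstratified and futility stops count as failures.

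| Accrual | Poor-risk share | Poor vs intermediate HR | Fixed 700: plain / stratified | Gain | Adaptive: plain / stratified | Gain |
|---|---|---|---|---|---|---|
| 2 yr | 20% | 1.5 | 79.1 / 79.9 | 0.8 | 66.1 / 66.6 | 0.5 |
| 2 yr | 35% | 1.5 | 78.0 / 79.1 | 1.1 | 64.5 / 65.5 | 1.0 |
| 2 yr | 20% | 2.0 | 77.1 / 79.7 | 2.6 | 64.2 / 66.0 | 1.8 |
| 2 yr | 35% | 2.0 | 75.9 / 79.2 | 3.3 | 63.9 / 66.5 | 2.6 |
| 2 yr | 35% | 2.5 | 72.9 / 79.3 | 6.4 | 60.6 / 65.4 | 4.8 |
| 7 yr | 20% | 1.5 | 83.8 / 84.4 | 0.6 | 78.1 / 78.5 | 0.4 |
| 7 yr | 35% | 1.5 | 83.7 / 84.7 | 1.0 | 77.9 / 78.7 | 0.8 |
| 7 yr | 20% | 2.0 | 81.7 / 84.2 | 2.5 | 76.0 / 77.7 | 1.7 |
| 7 yr | 35% | 2.0 | 79.8 / 84.1 | 4.3 | 74.5 / 77.1 | 2.6 |
| 7 yr | 35% | 2.5 | 75.5 / 83.2 | 7.7 | 70.6 / 76.0 | 5.4 |

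The differences between the two tests are the relevant figures. The absolute levels move with the assumed accrual. A separate simulation of the same comparison gave about 1 point at 1.5, 3-5 at 2.0 and 4-6 at 2.5, with no loss when the factor was not prognostic. Type I error stayed near 5% (4.7% plain, 4.9% stratified).

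**Step 3: type of ICI combination.** In the fixed design with 2-year accrual, power was 79.9 / 80.6 (plain / stratified) at a hazard ratio of 1.3 and 80.5 / 80.4 at 1.15. With 7-year accrual it was 83.6 / 84.3 and 84.9 / 84.9. The gain is 0 to 0.7 points, which is negligible.

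**Step 4: what the gain is worth.** Events needed scale with (z_alpha + z_beta)². For the two 2-year, fixed-design rows at HR 2.0:

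- 77.1% to 79.7%: (1.645 + 0.831)² / (1.645 + 0.742)² = 1.076.
- 75.9% to 79.2%: (1.645 + 0.813)² / (1.645 + 0.703)² = 1.096.

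That equals 8-10% more events, or about 53 to 67 of 700 patients if events scale with sample size.

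**The case against.** **The test is never called unstratified.** That reading comes from plain wording in a condensed article, and a full protocol or SAP may name strata. This stands as a caution. But section 2.8 does not defer the test: it fixes the test, side and threshold, section 2.7 attaches a power to it, and section 2.8 names covariates for quality of life. The mismatch with section 2.4 on timing is in the text either way.

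**A reader might infer that the 79.8% is wrong.** The documents do not support that. The figure reproduces under one hazard per arm. The shortfall arises only if risk groups differ in survival and 0.7975 is the within-group effect. Section 2.7 derives it from whole-population medians, and section 2.8 describes the ITT result as an average effect. If 0.7975 is the population-level HR, the plain test hides no loss, and stratifying would be an improvement, not a repair.

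**The size rests on outside assumptions.** This also stands. The document gives neither the prognostic hazard ratio nor the poor-risk share. The 43% and 11% in the Introduction are survival figures for poor-risk patients in earlier trials, not shares of this population. Requiring 6 months without metastatic progression may also weaken the effect of risk group by the time of randomisation.

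**A reader might also infer that leaving out ICI type costs power.** In the range tried it does not.

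**Changing the final test touches the simulated design.** True, but the interim rules can stay as they are, and re-simulating the final test is cheap.

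**Conclusion.** The point holds as a recommended improvement together with one inconsistency to settle. Section 2.8 names a deciding test that cannot carry the timing variable of section 2.4 and does not use a risk group known at entry.

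If risk group is prognostic and HR 0.7975 holds within groups, with 20-35% poor risk, the plain log-rank gives up about 1 point of power at a poor-versus-intermediate HR of 1.5, 2-5 points at 2.0 and 4-7 points at 2.5. One scenario (fixed design, 7-year accrual, 35% poor risk, HR 2.5) reached 7.7. With the interim looks applied, the gains lie at or just below the lower end of these ranges for HR 1.5 and 2.0, and at about 5 points for HR 2.5. If the factor is not prognostic, nothing is lost by stratifying. The case concerns risk group and timing; type of ICI combination is incidental.

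**What to change.** Before any outcome analysis, state in section 2.8 that the final one-sided 0.05 test for OS is one of the following:

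- a log-rank stratified by risk group (intermediate or poor), with type of ICI combination as an optional further stratum; or
- the equivalent Cox test adjusted for risk group and timing of randomisation.

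The Cox option settles the mismatch with section 2.4 directly. If the stratified log-rank is chosen, sections 2.4 and 2.8 should say where timing enters, for example in the Cox model. Report the HR from the matching Cox model and keep the plain log-rank as a sensitivity analysis. The threshold, sample size, follow-up and interim rules stay unchanged.

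The costs are small. The reported HR becomes a within-stratum HR, patients with unknown risk group need their own stratum, and power and type I error of the final test should be re-simulated with the existing interim rules.

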### Primary and secondary endpoints

2.2

The primary clinical endpoint is OS, defined as the time from randomisation to death of any cause. The main secondary endpoint is the objective response rate in the primary tumour before local therapy, assessed by a computed tomography scan. Other secondary endpoints are long-term follow-up of quality of life (QoL) using the Dutch validated European Organisation for Research and Treatment of Cancer (EORTC) Quality of Life Questionnaire (QLQ-C30) [27] and Clavien-Dindo classification of surgical morbidity [28]. Both follow-up of QoL and surgical morbidity are part of the standard PRO-RCC data collection schedule.

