### Experimental intervention

2.5

The experimental intervention consists of (partial) CN or any ablative local therapy between 6 mo and 1.5 yr after the start of systemic treatment. All types of ablative local therapies are allowed as a substitute for CN, including magnetic resonance imaging–guided stereotactic radiation. The patients’ physician chooses the treatment plan and the modality used for tumour ablation. Randomisation occurs after at least 6 mo of ICI combination therapy, as stated in Figure 2. Patients who discontinue their first-line treatment due to progression at metastatic sites in the timeframe between randomisation and local therapy are disqualified for local treatment but continued in the TwiCs study in order to be part of the intention-to-treat (ITT) analysis. The same applies for patients who are randomised to the experimental arm but who refuse local treatment. All these patients will be treated according to the SOC. Patients in the experimental arm will be asked for additional sampling of blood after the local intervention.

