### SOC treatment

2.6

Patients randomised to the control arm will receive first-line ICI combination therapy according to current guidelines, which do not routinely recommend CN in this setting [20]. Patients with controlled systemic disease but progression of the primary tumour can be offered deferred CN at the discretion of the treating physician. Likewise, patients with a complete response at metastatic sites who can be rendered disease free by deferred CN are not excluded from an intervention if the treating physician considers nephrectomy in the patient’s best interest. These patients remain in the TwiCs study for the ITT analysis.

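### On its usual reading, the added per-protocol survival analysis selects experimental patients on what happens after randomisation and so biases the HR in favour of local therapy

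*Protocol article*

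**What the plan says.** All references are to the protocol article.

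- **Time zero (2.2).** "The primary clinical endpoint is OS, defined as the time from randomisation to death of any cause".
- **When local therapy is given (2.5).** The intervention is (partial) nephrectomy or "any ablative local therapy between 6 mo and 1.5 yr after the start of systemic treatment". Section 2.4 places randomisation 6 to 18 months after the start of systemic treatment.
- **Who does not get it (2.5).** Patients who stop first-line treatment because of metastatic progression "in the timeframe between randomisation and local therapy are disqualified for local treatment but continued in the TwiCs study"; the stated purpose of keeping them is the ITT analysis. "The same applies for patients who are randomised to the experimental arm but who refuse local treatment".
- **Controls who do get it (2.6).** Controls whose primary tumour progresses while systemic disease is controlled may be offered deferred nephrectomy, and "patients with a complete response at metastatic sites who can be rendered disease free by deferred CN are not excluded from an intervention". They too are kept for ITT.
- **Analyses (2.8).** ITT is the basis, with a treatment-policy strategy for noncompliance. Then: "In addition, a per-protocol analysis will be performed", and "ITT and per-protocol subgroup analyses will be performed for subgroups based on the type of local treatment and type of systemic treatment".

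The article gives no per-protocol set, time zero, landmark, time-dependent exposure or weighting.

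**The concern.** An experimental patient can receive local therapy only by staying alive and free of metastatic progression until the day it is given. If per-protocol membership means having received it, and survival is still counted from randomisation, each included experimental patient carries a stretch of guaranteed survival and has been screened for good early prognosis. Controls pass no such screen: their early deaths and early progressors all count. This is guarantee-time (immortal-time) bias, and it favours local therapy.

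The control side probably adds to it. Removing controls who had nephrectomy would remove patients with controlled systemic disease, some of them complete responders at metastatic sites.

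What is at stake is interpretation. Section 2.7 expects 15% refusal and also models 25%, so the per-protocol figure is a natural place to look for the effect of treatment actually given. A null ITT result could then sit beside an apparently favourable per-protocol HR that selection alone had produced. Per-protocol subgroups by type of local treatment have the same fault, since that type is known only after randomisation and, in principle, only in the experimental arm.

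**Working it through.** **1. The plan's own figure.** Section 2.7 gives 79.8% power for the final one-sided 5% log-rank test at HR 0.7975 with 700 patients. Schoenfeld events for 80% power: 4 × (1.645 + 0.842)² / (ln 0.7975)² = 24.73 / 0.0512, or 484. With a control hazard of 0.0043 per week, 350 per arm, 5 years' minimum follow-up and an assumed 2-year accrual, 487 events are expected and power is 80.3%. The plan's figure reproduces, so the survival inputs are usable below.

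**2. Inputs for the check.** From the article: 350 per arm, control median overall survival (OS) 36 months, 15% refusal, 5-year follow-up for all, one-sided 5%. Assumed: no effect of local therapy, refusal unrelated to prognosis, the wait from randomisation to local therapy, accrual, and the course of progression. Two models were used:

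- *Model A:* OS is the sum of two equal exponential times (to progression, then to death), each with rate 1.678/156 per week, which gives a median of 156 weeks. Accrual is 2 per week.
- *Model B:* illness-death model with median progression-free survival of 12, 18 or 24 months from randomisation, calibrated to median OS 36 months. Accrual is 36 months.

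Each scenario used 1,500 trials. The experimental set is non-refusers alive and progression-free at the time of local therapy. All controls are kept.

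**3. How many are screened out.** With exponential progression-free survival of median m months, the share of experimental non-refusers lost before a wait of d months is 1 − 0.5^(d/m). For m = 18: d = 3 gives 10.9% and d = 6 gives 20.6%. If only deaths are lost (median 36), the shares are 5.6% and 10.9%.

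**4. Per-protocol HR when the true HR is 1.**

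| Wait, same for all | Model A: HR (one-sided p<0.05) | Model B: HR (one-sided p<0.05) |
|---|---|---|
| 1 month | 0.97 (10%) | 0.97 (9-10%) |
| 3 months | 0.91 (28%) | 0.92 (22-25%) |
| 6 months | 0.84 (65%) | 0.83-0.84 (58-63%) |

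Removing only early deaths gives 0.93-0.94 at 3 months and 0.86-0.88 at 6 months.

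**5. Waits that fit the window.** Randomisation and local therapy both fall in months 6 to 18, so the wait lies between 0 and 12 months, and nobody randomised after month 12 can wait 6 months. Spreading waits over this window gave HR about 0.91 with 28% rejection. A repeat with randomisation uniform over months 6 to 18 and local therapy uniform over what remains (mean wait (18 − 12)/2 = 3 months) gave 0.92-0.93 with 22-25%, across both models.

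**6. Controls on the method (model B).** ITT: HR 1.00, 6.2% rejection (simulation standard error about 0.6 points). Dropping refusers only: HR 1.00, 4.8%. The bias therefore comes from requiring progression-free survival up to treatment. A landmark requiring both arms to be alive and progression-free, with the clock restarted there, gives HR 0.995-1.011 and 4-6% rejection.

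**7. Not covered by the planned covariate.** Section 2.4 adds the timing of randomisation to the analysis. That is the time from systemic start to randomisation, not the wait afterwards, so it does not remove the bias.

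**The case against.** The strongest reply is that the article never says who is per-protocol, and that an article may leave this to the full protocol or analysis plan. Another reading fits the text. Section 2.7 uses noncompliance for refusal, and a patient disqualified after metastatic progression has followed the rule in section 2.5. A set that drops only refusers would show no bias if refusal is unrelated to prognosis (step 6). This stands as a limit: the biased form is not fixed by the text, and an unseen plan may contain a valid method. It does not remove the point. Section 2.5 treats progressors and refusers alike, as kept for ITT, and section 2.8 commits to per-protocol subgroups by type of local treatment, which rest on treatment received after randomisation.

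It is also fair that the size depends on a wait the article does not state, that a uniform 6-month wait is impossible for late-randomised patients, and that the control-side exclusion was not simulated. The rejection rates borrow the threshold of the final efficacy test; section 2.8 attaches no test to the per-protocol analysis.

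Two stronger readings should be resisted. A reader might infer that the analysis will show a benefit even if local therapy does nothing. The HR is biased below 1, but at waits of 1 to 3 months 72-91% of null trials would not reach one-sided significance. A reader might also infer that the trial's conclusion is compromised. It is not: efficacy rests on the ITT log-rank test and interim stopping on the posterior boundaries in Table 2.

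**Conclusion.** The point holds in conditional form. If the per-protocol set is experimental patients who received local therapy against controls, timed from randomisation, the HR is biased in favour of local therapy. The direction is firm. The size rests on assumed waits: negligible to small at 1 month (about 0.97), moderate at 3 months or with waits spread over the permitted window (about 0.91-0.93), and large at 6 months (0.83-0.84). The last is about the HR of 0.84 that section 2.7 models as a diluted real effect, but not every patient could wait that long. Dropping controls who had nephrectomy would probably push the same way; this was not quantified, and section 2.7 puts such patients at about 7% of controls. With the primary ITT analysis unaffected, this is a moderate fault in a supportive analysis and its subgroups.

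**What to change.** Do not define the per-protocol set, or its subgroups, by treatment received after randomisation while keeping the clock at randomisation. To estimate the effect of receiving local therapy, use one of these:

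- **Complier-average estimate**, with the randomised offer as instrument: the ITT difference in 5-year restricted mean survival divided by the between-arm difference in the proportion receiving local therapy, with a bootstrap confidence interval. At the plan's own rates the divisor would be at most 0.85 − 0.07 = 0.78, and lower once patients lost while waiting are counted. The 5-year follow-up of all patients supports this. It assumes that the offer affects survival only through the treatment received.
- **Clone-censor-weighting**, with the same eligibility in both arms.
- **A landmark** that applies the same alive and progression-free rule to both arms and restarts the clock there.

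Label the result supportive, and do not compare subgroups by type of local treatment with all controls from randomisation. The cost is analysis-plan wording and a little more analysis. The estimate will be less favourable than the naive one and its confidence interval wider.
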